## Abstract

**Background**: There are numerous barriers leading to a high unmet need for family planning and contraceptives (FP/C).  These include limited knowledge and information, poor access to quality services, structural inefficiencies in service provision and inadequately trained and supervised health professionals. Recently, social accountability programs have shown promising results in addressing barriers to accessing sexual and reproductive health services. As a highly complex participatory process with multiple and interrelated components, steps and actors, studying social accountability poses methodological challenges. The Community and Provider driven Social Accountability Intervention (CaPSAI) Project study protocol was developed to measure the impact of a social accountability intervention on contraceptive uptake and use and to understand the mechanisms and contextual factors that influence and generate these effects (with emphasis on health services actors and community members).

**Methods**: CaPSAI Project is implementing a social accountability intervention where service users and providers assess the quality of local FP/C services and jointly identify ways to improve the delivery and quality of such services. In the project, a quasi-experimental study utilizing an interrupted time series design with a control group is conducted in eight intervention and eight control facilities in each study country, which are Ghana and Tanzania. A cross-sectional survey of service users and health care providers is used to measure social accountability outcomes, and a cohort of women who are new users of FP/C is followed up after the completion of the intervention to measure contraceptive use and continuation. The process evaluation utilizes a range of methods and data sources to enable a fuller description of how the findings were produced.

**Conclusion**: This complex study design could provide researchers and implementers with the means to better measure and understand the mechanisms and contextual factors that influence social accountability processes in reproductive health, adding important findings to the evidence base.

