**Setting**	Intervention and control facilities	Intervention and control facilities	Intervention facilities	Intervention facilities N.B. The context mapping activity will be undertaken in both intervention and control sites (three interviews per district).
**Timing** *(N.B. Month 1–4* *was for preparing* *the study)*	Baseline: Month 5 Interim: Month 17 End-line: Month 29	Intake: Month 10–12 Check-up: Month 16–18 Follow up: Month 22–24	Pre-test: Month 5 Post-test: Month 17	8–12 data points tied to key events in the intervention facilities between Month 6 and Month 18. Eight events at four intervention facilities per country.
**Data sources**	Facility audit of FP/C facilities	Prospective cohort follow-up of new users	Cross sectional survey using a questionnaire of psychometric scales with women accessing FP/C and health care providers in intervention sites	Context mapping (three per district for both the intervention and control sites) In-depth interviews (three per observation) Observations (8–12 per process evaluation site) Document review

i. 
*Capturing changes in contraceptive uptake:* A quasi-experimental study utilizing an interrupted time series design with a control group (ITS-CG) is conducted to determine the actual number of new users of contraception amongst women 15–49 years old in eight intervention and eight control facilities per country. New users are defined as: never used an FP/C method (new acceptors); are switching from a traditional to a modern FP/C method (additional users); or are re-starting an FP/C method after a period of not using it for at least six months (additional users). The facility is the sampling unit.Contraceptive uptake in both the intervention and control arms is measured by comparing the level changes and trends over time during the study period. The numerator of the rate is measured using the facility audits provided by the intervention and control facilities, while the denominator of the rate, measured at the community level, is the number of women of reproductive age in the catchment area for the facility. The facility catchment area definitions used are those provided by Ghana Health Service in Ghana and the Ministry of Health in Tanzania. The catchment area study population size is collected from official statistics calculated on a yearly basis and, based on trend analysis, is expected to remain roughly constant throughout the study duration.ii. 

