*Capturing changes in contraceptive use*: A cohort of women, 15 to 49 years of age, who are new users of contraception and who are accessing FP/C services at the study facilities are tracked across both intervention and control facilities to measure changes in behaviors around contraceptive use such as method continuation, switching, contraceptive decision making, and client satisfaction. Method contraception discontinuation rate (first use) is estimated using a prospective cohort study design. The outcome of interest is time from starting modern contraceptive method use until when use is discontinued.Contraceptive method continuation (proportion of women in a cohort using the same contraceptive method after one year) and contraceptive switching (proportion of women in a cohort changing method within one year of initiation, out of those using any method at baseline/proportion of women, because they were not satisfied with the previous one) are measured.iii. 
*Evaluating effects of the social accountability process:* To capture the intermediate outcomes outlined in the ToC (see
Figure 1), such as empowerment of women and health providers and expansion of negotiated spaces, a cross-sectional survey using accountability-related psychometric scales is conducted at pre- and post-intervention phases. One survey is conducted with women accessing FP/C services in health facilities in the catchment areas where the social accountability intervention is being implemented. Another survey is conducted with health workers providing FP/C services in health facilities in the catchment areas where the social accountability intervention is being implemented.iv. 

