*Contraceptive uptake:* For sample size calculations, it is assumed that, at pre-intervention, the mean number of new users per facility per month would be similar in both the intervention and control arms. It is further assumed that in the control arm, the pre-test and post-test mean number of new users per facility per month, per arm will remain the same. Study sample size and power were estimated in two ways: with the facility as the unit of measurement for Poisson regression, and with the monthly data points as the unit of measurement for time series regression. With the facility as the unit of sampling and of analysis, and assuming two-time points of interest, at pre-test (or baseline) and at post-test, different sample size estimates were computed using a two-sided t-test with Type I error at 5% level, statistical power at 80%, and assuming equal variance. These various sample size estimates are provided assuming a constant denominator (included as an offset in the Poisson model) and a pooled variance for mean number of new users at pre-intervention in both arms of between 100 and 200 new users per facility, per month, and a difference in uptake per facility per month, at post-intervention of between 60 and 200 new users. Approximately, five to eight facilities are needed per intervention or control group to detect an approximately two-fold increase in the rate of new users with 80% power and allowing for a 5% Type I error. The monthly data points were used as the unit of analysis and, based on effect size and time periods, the simulation-based power calculation provided by Zhang
*et al.*, 2011
^39^ was used. Assuming an effect size of 2.0 (derived from 100 new users in control group and 200 new users in intervention group and a pooled standard deviation of 50) and an autocorrelation of up to 0.3, a total of 12 data points – the equivalent to six monthly pre-intervention data points and six monthly post-intervention data points – would be needed to achieve 80% power at p=0.05 statistical significance level
^39^.ii. 

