^43^. The collected data are entered at each country using a customized web-based electronic data capture (EDC) system using the OpenClinica Enterprise platform for entering, cleaning and tracking the study data, developed by the WHO Department of Sexual and Reproductive Health and Research Statistics and Informatics Services (WHO/SRH/SIS) team in Geneva. The web-based data capture system is designed to ensure that only authorized staff can enter, change, or view data. The local study data management teams were trained in data collection, online data entry, and data management using the EDC system. The SRH/SIS team liaises with the local study team to coordinate and track case report form (CRF) completion and data queries.ii. 
*Contraceptive use:* A cohort of women new to using contraception in both intervention and control facilities is followed-up over a 12-month period (starting at the end of the main intervention steps, i.e. end of step 6). Data is collected in real time using tablet-based standardized interview questions developed using OpenClinica Participate. The EDC system performs edit checks during the data capture process to notify immediately of potential errors and inconsistencies. The local study team keeps an updated log of screened and enrolled study participants.The two main instruments (intake and follow-up survey) collect data from new users of family planning services at the facility (see CaPSAI_ITS_CUI_FUI
*Extended data*)
^42^. A mid-term check-up interview is used to reduce loss to follow-up and estimate continuation by confirming if the participants are still using a method and which method it is. The cohort study instruments are adapted from existing tools capturing demographic characteristics and contraceptive use
^44^, client satisfaction
^45^, contraceptive continuation
^46^. Exposure to or knowledge of the community and provider driven social accountability intervention is also captured.iii. 
*Social accountability intermediate outcomes:* A cross-sectional survey using a questionnaire of accountability-related psychometric scales (see CaPSAI_XSU_XPV,
*Extended data*)

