*Contraceptive uptake:* All potential confounders associated with all the facilities enrolled are recorded. An ITS segmented Poisson regression model will be used to estimate both the level changes in first-use modern contraception rate and changes in time trends for the rate of modern contraception first-use rates per 10,000 women-months, after the introduction of the intervention. The generalized estimating equation (GEE) Poisson segmented regression model will allow adjustment for correlation due to repeated observations from the same facilities, while also adjusting for important baseline family planning facility characteristics. ii. 
*Contraceptive use:* For categorical variables frequencies and percentages will be reported, and for quantitative variables number of subjects, means, standard errors, medians, interquartile range, minima, and maxima will be reported. Rate of loss to follow-up for the one-year follow-up period will be computed by intervention arm. The one-year cumulative method discontinuation and method switching rates will be compared between the intervention and control arms. Because of the clustered nature of the outcomes, with intervention package designed at the cluster level, all time-to-event outcomes including loss to follow-up, method discontinuation, and method switching, will be analyzed with hazard ratios estimated from the marginal Cox model and/or shared Frailty models. The model will be adjusted for baseline potential confounders at participant and/or facility level. Two-sided tests, 5% significance levels and 95% confidence intervals will be used for all relevant parameters. Statistical Analysis System (SAS) Version 9.4 and R Version 3.3.3 software packages will be used for the statistical analyses. Open-ended questions will be listed and coded for meaningful comparisons of their distribution.iii. 

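### Cohort women enter as new users after intervention steps 1–6, so the discontinuation hazard ratio mixes who starts with how long they continue

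*Protocol article*

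**What the plan says.** All references are to the Protocol article, Study design and methods, unless stated.

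- **Start of the cohort** (5 Data collection, ii): follow-up runs for 12 months, "starting at the end of the main intervention steps, i.e. end of step 6".
- **Calendar** (Table 3): for the cohort, "Intake: Month 10–12 Check-up: Month 16–18 Follow up: Month 22–24"; for the process evaluation, "8–12 data points tied to key events in the intervention facilities between Month 6 and Month 18". The Abstract says that the cohort "is followed up after the completion of the intervention to measure contraceptive use and continuation".
- **Who enters** (3 Study design, ii): women aged 15–49 "who are new users of contraception and who are accessing FP/C services at the study facilities", in both arms.
- **What the intervention is meant to raise** (4 Sample size, i): uptake is sized "to detect an approximately two-fold increase in the rate of new users with 80% power".
- **Analysis** (6 Data analysis, ii): discontinuation, switching and loss to follow-up are compared between arms by marginal Cox and/or shared frailty models. "The model will be adjusted for baseline potential confounders at participant and/or facility level".
- **Pre-intervention data**: the facility audit is timed "Baseline: Month 5 Interim: Month 17 End-line: Month 29", and monthly counts of new users start six months before baseline (5 Data collection, i). Participant data in the cohort start with the intake survey.
- **Study limitations** (Discussion): for the cohort, these name loss to follow-up, the numbers needed, willingness to participate and recall. Entry after exposure is not among them.

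**The concern.** A between-arm hazard ratio isolates an effect on continuation only if the women at risk in the two arms are alike apart from the intervention. Here entry to the risk set is itself something the intervention is designed to change. By Months 10–12 the intervention communities have had mobilisation, health and rights education, prioritisation and joint action planning. Women drawn into contraception by those steps have no counterpart in the control cohort, and they may be more or less likely to stop than other starters. No cohort recruited before the intervention is available to subtract such a difference.

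The word baseline adds a second difficulty. Any participant-level covariate measured at intake is measured after exposure. Some intake measures, such as method chosen, satisfaction or awareness of the intervention, could lie on the theory-of-change path from better services to continued use. Adjusting for those would remove part of the effect being sought.

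Contraceptive use is listed with uptake among the primary outcomes in Table 4, and the stated aim is to measure the intervention's effect on both. A reader would naturally take the hazard ratio as an effect on continuation.

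**Working it through.** **1. Order of events.** Intervention events run over Months 6–18, intake over Months 10–12, and final follow-up over Months 22–24. Steps 1–6 precede intake. Steps 7 and 8, the three- and six-month follow-up meetings, come after it. The intervention is therefore well under way at intake but not finished, despite the Abstract's wording.

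**2. The plan's own figure.** Inputs from 4 Sample size, ii: hazard ratio 0.7, control discontinuation 40% (within the stated 30–60%), two-sided 5%, 80% power, 20% exponential loss, design effect 2.0.
- Schoenfeld events: 4 × (1.96 + 0.842)² / (ln 0.7)² = 247.
- Hazards: control −ln 0.6 = 0.511; intervention 0.7 × 0.511 = 0.358; loss −ln 0.8 = 0.223.
- One-year event probability, h/(h + 0.223) × [1 − exp(−(h + 0.223))]: 0.362 in control and 0.271 in intervention, mean 0.317.
- Women per arm: 247 / 0.317 / 2 ≈ 390; times 2.0 ≈ 780.

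This is within 3% of the stated 800. The sizing treats the hazard ratio as a pure continuation effect.

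**3. How far starter mix alone can move the hazard ratio.** Let R be the ratio of new users at intake with the intervention to without it. The share of additional starters is f = 1 − 1/R. Let k be their stopping hazard relative to other starters. **k is not in the protocol and is assumed.** The cohort is taken to be representative of starters, and the other starters to be alike in both arms.

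With no effect on continuation and 40% control discontinuation:
- one-year continuation in the intervention arm is S = (1 − f) × 0.6 + f × 0.6^k;
- apparent hazard ratio ≈ −ln S / 0.511.

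| Uptake rise at intake | f | k | S | Apparent HR |
|---|---|---|---|---|
| two-fold | 0.50 | 0.5 | 0.687 | 0.73 |
| two-fold | 0.50 | 2 | 0.480 | 1.44 |
| one third | 0.25 | 0.5 | 0.644 | 0.86 |
| one third | 0.25 | 2 | 0.540 | 1.21 |
| 10% | 0.091 | 1.25 | 0.593 | 1.02 |
| 10% | 0.091 | 1.5 | 0.588 | 1.04 |

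The large-sample Cox estimate over one year with 20% loss, across control discontinuation of 30–60%, gives nearly the same values:
- f = 0.5: 0.73–0.74 (k = 0.5) and 1.41–1.46 (k = 2);
- f = 0.25: 0.86–0.87 (k = 0.5) and 1.19–1.22 (k = 2).

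**4. Thresholds in the upper case (f = 0.5).** With no true effect, k of about 0.43–0.46 alone produces the planned hazard ratio of 0.7. With a true hazard ratio of 0.7, k of about 1.90–1.98 hides it completely.

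**The case against.** **The mix may have changed little by intake.** Step 6 only produces an action plan for the next 6 to 12 months, and Table 2 expects change from health services actors at step 7. The two-fold rise is the difference used to size uptake, not a forecast for Months 10–12. This stands. A reader might infer that half the intervention cohort would be additional women. The protocol does not say so, and f = 0.5 is an upper case. It does not remove the problem, because community mobilisation and education come before intake and could already affect who attends.

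**The plan does not say it adjusts for mediators.** This also stands. A reader might infer that method, counselling or satisfaction will be in the model. The protocol names no covariates, and an article commonly leaves that list to the analysis plan. Facility covariates could come from the Month 5 audit. What the text does fix is that participant-level values are collected at intake, after exposure began.

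**The comparison is legitimate as it stands.** Discontinuation among women who started in each arm is a meaningful programme result. Agreed, provided that it is reported as that and not as an effect on continuation alone.

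**Stratifying is not a cure.** Additional and other starters occur within every new-user category, so the selection problem is reduced, not removed.

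**Conclusion.** The point holds as a limit on what the hazard ratio means. Entry follows steps 1–6, entry is an outcome of the intervention, there is no pre-intervention cohort, and the limitations section is silent on this. The planned Cox or frailty contrast therefore cannot separate a change in who starts from a change in how long they continue.

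Neither size nor direction can be taken from the document. With no effect on continuation, starter mix alone gives a hazard ratio of about 0.73 to 1.46 in the upper case (half of starters additional, k from 0.5 to 2), and about 1.02–1.04 for a 10% rise in uptake with k of 1.25–1.5. A reader might conclude that the design hides a benefit. That needs k above 1; with k below 1 the same mechanism manufactures a benefit. The sample size of 800 per arm is not in question here.

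**What to change.** 1. In 6 Data analysis, ii, limit the primary adjustment set to Month 5 facility-audit values and participant characteristics the intervention cannot have changed, such as age and other demographics collected at intake. Keep method chosen, satisfaction, counselling and exposure to the intervention out of it.
2. Stratify or standardise the arm comparison by the three new-user categories in 3 Study design, i (never used; traditional to modern; re-starting after at least six months), and report starter mix by arm.
3. Add a sensitivity bound using the formula above, with k on both sides of 1. R at intake can be informed by the monthly new-user counts that the study already collects.
4. Describe the hazard ratio as a comparison among women who started in each arm. List entry after exposure under Study limitations, and align the Abstract's account of cohort timing with the end of step 6.

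**Cost:** wording and analysis only, provided that intake records the new-user category; the article does not show the instrument. There is a slight loss of precision and a more modest claim. Unmeasured differences between starters, such as motivation, remain.

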**6. Interface meeting and joint** **action planning**	The implementation partner then holds a joint meeting between the community, the service providers and health services actors (duty bearers). Following the presentation of results from the prioritization meetings, the community groups and the service providers will aim to reach consensus on the ranking of the priority items and the actions required to address them. An action plan with assigned roles and responsibilities will be developed for the following 6- to 12-month period.
**7. First follow-up meeting** **with community and duty** **bearers at three months**	Priority areas and action items will be followed up with both the community and service providers. It is at this stage that change is anticipated on the part of health services actors and remedial actions have taken place which should be demonstrated in the monitoring activities. For any unresolved issues, these meetings present an opportunity to involve higher level duty bearers or third-party groups (media/politicians) to increase the pressure to act.
**8. Second follow-up meeting** **with community duty bearers** **at six months**	A second follow-up meeting will enable the monitoring of longer-range outcomes and on the remedy of unresolved issues raised in the first follow-up meeting. The community and service providers will continue to monitor the action plan for changes in relation to agreed priority areas.

2
Study setting

The intervention targets community members, health professionals and other duty bearers at both the community and facility level. Study outcomes are measured at the facility level.

Ghana and Tanzania were selected as the study countries based on the following selection criteria: existence of a national civil society organization (CSO) partner with local experience of delivering a social accountability intervention with the eight steps; low modern contraceptive prevalence rate; availability of contraceptive services at the point of contact by the client at no cost or where cost is not a barrier to access; an enabling environment in terms of the potential for the health system to respond to the social accountability activities; and the existence of formal structures linking the community with the health system (e.g. health committees). 

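### The uptake model measures level and trend change from the introduction of a phased intervention, so an effect that builds up later is split misleadingly between the two terms

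*Protocol article*

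**What the plan says.** All references are to the Protocol article, Study design and methods.

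- **Model.** Data analysis, item i, specifies a segmented Poisson regression with GEE and gives it two targets. The second is worded as "changes in time trends for the rate of modern contraception first-use rates per 10,000 women-months, after the introduction of the intervention". The first is a step in the rate, where the model is to "estimate both the level changes in first-use modern contraception rate". No lag, transition period or implementation segment is mentioned.
- **Duration of the intervention.** Table 3 schedules the process evaluation as "8–12 data points tied to key events in the intervention facilities between Month 6 and Month 18".
- **When change is expected.** Table 2 says of step 7, the first follow-up meeting: "It is at this stage that change is anticipated on the part of health services actors and remedial actions have taken place". The timing in its row label is "bearers at three months".
- **End of step 6.** Data collection, item ii, has cohort follow-up "starting at the end of the main intervention steps, i.e. end of step 6". Table 3 puts cohort intake at Months 10 to 12.
- **Monthly series.** New users are recorded monthly from six months before baseline (Month 5) to end-line (Month 29).

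**The concern.** A level-plus-trend model treats the interruption as a point at which the rate can jump and its slope can change. Here, introduction starts a sequence of meetings. The joint action plan comes only at step 6, and the follow-up at which providers' remedial action should be visible comes at step 7. If the interruption is at introduction, the early months are modelled as fully post-intervention although the effect is still building.

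A straight line cannot follow a flat stretch and then a step. It starts too low and ends too high. The level change is then understated, and the trend change suggests continuing growth that does not exist. Both are planned results for uptake, which Table 4 lists among the primary outcomes. The other quantitative components use later reference points: the cohort starts after step 6, and the post-test survey after step 8.

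**Working it through.** **1. Timeline**

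- Pre-intervention: six months before Month 5, plus Month 5, gives Months -1 to 5, or 7 points.
- From introduction to end-line: Months 6 to 29, or 24 points.
- End of step 6: about Month 10 to 12, from cohort intake.
- Step 7: three months later (the meeting's timing is read as counted from step 6), so about Month 13 to 15. The post-test survey is at Month 17 and follows step 8, the six-month meeting. That suggests step 7 by about Month 14 and makes Month 15 the late end.
- Months counted as post-intervention before onset: 4 for onset at Month 10, 7 for Month 13, 9 for Month 15.

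**2. The plan's own figures**

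The Sample size section states five to eight facilities per group for about a two-fold increase. Taking 100 against 200 new users and SD 50 from its time-series calculation, the normal approximation is n = 2(1.96 + 0.84)² × (50/100)² = 3.92, so 4 per arm. The exact two-sided t-test has power 0.79 at n = 5 and 0.88 at n = 6, so 6 per arm, within the stated range. The time-series calculation assumes the doubling holds over six post-intervention months. Counted from Month 6, those are Months 6 to 11, all before step 7.

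**3. What the planned model returns for a delayed doubling**

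The model is log E(Y_t) = log N + b0 + b1·t + b2·P_t + b3·P_t·(t − 6), with P_t = 1 from Month 6. The control arm is flat, as the Sample size section assumes, so the controlled contrast equals that of the intervention arm. Noise-free counts are 100 per month before onset and 200 from onset.

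| Onset (month) | Level rate ratio, exp(b2) | Share of log effect, b2/ln 2 | Trend ratio per month | Fitted ratio at Month 29 |
|---|---|---|---|---|
| 6 | 2.00 | 100% | 1.000 | 2.00 |
| 10 | 1.46 | 55% | 1.019 | 2.26 |
| 13 | 1.18 | 23% | 1.031 | 2.37 |
| 14 | 1.10 | 14% | 1.034 | 2.39 |
| 15 | 1.03 | 5% | 1.037 | 2.40 |

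For onset at Month 13, the end-line value is 1.176 × 1.031^23 ≈ 2.37, against a true 2.00.

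**4. The effect is still in the model**

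For onset at Month 13, the true mean post-period ratio is (7 × 1 + 17 × 2)/24 = 1.708. The fitted values average 1.708 as well. Only the shape is wrong.

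**5. Softer onset (assumed shapes)**

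- Gradual rise over Months 10 to 13: level ratio 1.31 (39%). Over Months 12 to 15: 1.14 (19%).
- A share of the doubling present from Month 6 and the rest at Month 13: a 10% share recovers 32% of the log effect, 25% recovers 45%, and 50% recovers 65%.

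**6. Precision (simulation, approximate)**

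Eight facilities per arm, SD 50 per facility-month, autocorrelation 0.3, with facility-level least-squares coefficients compared by a two-sided 5% t-test:

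- Level term: power about 92% for an immediate effect, 7% for onset at Month 13.
- Trend term: about 14% for onset at Month 13, 16% for Month 15.
- Level term with Months 6 to 12 left out and the interruption at Month 13: unbiased (ratio 2.00, trend 1.00), but power only about 32%.
- Mean of Months 13 to 29 minus the pre-intervention mean, compared between arms: close to 100% for onset at Month 13 or 15, with no facility-specific drift assumed.

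**The case against.** **The interruption month is inferred.** The article names introduction, not a calendar month, and an analysis plan may set a date or a lag. That is fair as to Month 6 exactly. But the article does state introduction as the reference point, and that rule does not fit its own schedule. This is more than missing detail.

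**A reader might infer that nothing is expected to change before step 7.** Table 2 does not say so. It says remedial actions have taken place by then, so change can build between steps 6 and 7. The statement also concerns health services actors, while the outcome is women's uptake. The Theory of change section describes a demand-side route, and Table 2 places health and rights education at step 3. Earlier uptake is therefore possible, and the loss in the level term is then smaller.

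**A reader might infer that a working intervention would show a nil or negative effect.** The documents do not support that. Level and trend are planned together, neither is named as the sole effect measure, and the trend term takes up the delayed effect. Under the planned Poisson model, the level ratio stays above 1 for onset up to Month 15. What stands is that neither term describes a sustained doubling correctly, and that in the simulation each has low power for a late onset.

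**A transition period has a price, and a single mean contrast is partly a matter of preference.** Both points stand and shape the fix.

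**Conclusion.** The point holds as a mismatch between the stated reference point and the intervention's own schedule. For a sustained doubling starting between Months 10 and 15, the level term shows 55% down to 5% of the log effect, the trend term shows 2 to 4% monthly growth that is not real, and the end-line ratio is overstated at about 2.3 to 2.4. This rests on four assumptions: an interruption at about Month 6, step months derived from Tables 2 and 3 and the cohort's start, an abrupt onset, and a flat control arm. A gradual onset or early uptake from community education reduces the distortion. It does not show that the model would miss the effect altogether. It shows that the two planned terms, read separately, would misdescribe its size and timing.

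**What to change.** Before outcome modelling:

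1. Add a pre-specified implementation segment from introduction to a fixed scheduled date, for example the planned end of step 6. Use the same date for matched intervention and control facilities. A scheduled date is preferable to each facility's actual completion, which depends on how implementation went.
2. Report the controlled post-implementation versus pre-intervention rate ratio as the summary of the effect, alongside the level and trend terms.
3. Keep the model with the interruption at introduction as a sensitivity analysis.

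**What it recovers.** With the segment ending at Month 12, a doubling from Month 13 gives 2.00, and one from Month 15 gives (2 × 1 + 15 × 2)/17 = 1.88. With the segment ending at Month 10, the figures are (2 × 1 + 17 × 2)/19 = 1.89 and (4 × 1 + 15 × 2)/19 = 1.79.

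**Cost.** Only plan wording changes, because the monthly series is already collected. Post-intervention months fall from 24 to 17 or 19. A level term extrapolated across the gap from about 7 pre-intervention months is imprecise (power about 32% in the simulation), which is why the average contrast should be the summary. That contrast relies on the control arm to remove common time trends and does not correct for trends that differ between arms, so the level and trend terms should stay in the report.
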